### Intervention as Hypothesized

VPTs, which emerged from the VPU violence prevention strategy, were funded by the UK Home Office and Youth Endowment Fund (YEF), with the funding administered by the VPU and the Office of the South Wales Police and Crime Commissioner (Multimedia Appendices 2 and 3). Other HVIPs in the United Kingdom are volunteer-based, whereas the VPTs are nurse-led. The original implementation for VPTs was focused on identifying and supporting ED patients aged 11-25 years and on formalizing the identification of modifiable risks and vulnerabilities, supporting and advising patients, and to signposting to other services as appropriate. The VPTs also aimed to raise awareness of the service across ED clinical teams, with the aim of it becoming embedded within usual practice, and to train and upskill the clinical team to enable ascertainment and referral.

### Intervention as Implemented

Since November 2019, a collaborative VPT between the police and NHS has been operational in a South Wales Type I (consultant-led with resus) ED in Cardiff (the capital and largest city in Wales), and a second VPT began in an adjacent South Wales Type I ED in Swansea (the second-largest city in Wales) in January 2022. The VPTs initially sought to identify patients attending the ED due to violence. This remit was broadened, with VPTs subsequently receiving referrals from across the hospital and other community health care teams (eg, Minor Injury Units [MIUs] and General Practitioners).

The VPTs work with patients to gain an understanding of any circumstances contributing to their exposure to violence. They refer patients into care pathways (primary, secondary, and tertiary care, or third-sector organizations) to address any vulnerabilities or modifiable risks and can work alongside the third sector (nonprofit and charitable enterprise) to provide continual case management. The VPTs also train other staff within the hospital to improve the identification of violence-related injury, to support clinical staff interactions with patients, and to maintain safeguarding procedures. In addition, the EDs at Cardiff and Swansea take part in information sharing to tackle violence, in which anonymous data and intelligence regarding violent incidents are shared with community safety partnerships. These anonymized data enable partner resources to be best used for violence prevention, part of the Cardiff Model for violence prevention [39]. Following implementation, both VPTs expanded the age range of patients to encompass all age groups.

### Usual Care

Under usual practice, clinical ED staff are obliged to undertake safeguarding activities and provide for those attending due to violence. However, provision varies across EDs. Under usual practice, when people attend ED with an injury suspected to be caused by violence, their injuries are treated, and the patient is encouraged to contact the police or have the ED contact the police on their behalf. In cases of serious injury involving weapon use, the ED is obliged to contact the police irrespective of patient consent. In terms of general safeguarding, all patient-facing clinical staff are expected to have up-to-date safeguarding training and thus to carry out safeguarding tasks. Patients who are experiencing domestic violence can be referred to an Independent Domestic Violence Advocate (IDVA). Patients attending due to sexual assault can be referred to an Independent Sexual Violence Advocate (ISVA). For the 10 control EDs in Wales, 2 EDs have an IDVA, and 2 others have access to an IDVA not based in their ED. Furthermore, ED staff can also refer patients in a MARAC, typically in cases where the criteria are not met for formal safeguarding but the clinician suspects that something is not right. To facilitate, multiagency referral forms are filled out for children who require safeguarding, and Vulnerable Adult VA1 Forms (to support the referral of vulnerable adults) are completed for vulnerable adults who require safeguarding.

There are IDVAs based in the intervention EDs in Cardiff and Swansea. Only Cardiff has an ISVA. Broadly, usual practice focuses on children and victims of domestic violence. The patients eligible for VPT support are therefore those who are not eligible for support from the IDVA or ISVA and are typically older than 10 years. Apart from the IDVAs in control EDs, none have additional resources specifically dedicated to the role of supporting patients attending due to violence, relying mainly on existing clinical staff to support safeguarding within their departments. This may involve naming an existing member of staff as a safeguarding ambassador or having a nurse act as safeguarding lead for the department. Across Welsh EDs, some control EDs have provisions for victims of domestic violence that includes cards with the “Live Fear Free” helpline that they can give to patients experiencing domestic violence and who do not meet the criteria for a MARAC referral. Similarly, none of the control EDs have processes in place to support patients’ referral to outside agencies. If patients disclose that they are struggling with issues, or if staff suspect patients are experiencing an issue, then referrals will be made by clinical staff. However, this is not the same as VPT members working with patients to identify modifiable risks and vulnerabilities that contribute to their experience of violence. The VPTs in Cardiff and Swansea are therefore unique.

### Design and Conceptual Framework

A controlled longitudinal whole population (Wales, United Kingdom) natural experiment. The intervention in Cardiff began in November 2019, and in January 2022 in Swansea. Due to earlier changes in Emergency Department Data Set (EDDS) coding, these data are consistent and available from January 2012. Intervention data collection therefore begins in November 2019 and ends in August 2023, allowing a 12-month follow-up of patients until August 2024.

### Objective 1: Effectiveness

We hypothesize that engagement with the VPT will help patients overcome modifiable risks and receive support for vulnerabilities, and that therefore the intervention will reduce the recurrence of unscheduled ED attendance.

Other than those who are most seriously injured, patients will register at ED reception and be triaged, at which point the most appropriate pathway through ED will be determined. At reception patients will be asked about the reason for their attendance, including whether it was due to an assault, data that becomes a part of the Patient Management System (PMS) [39]. Patients may not disclose that the reason for their attendance was assault-related. They might be reluctant, the perpetrator may have accompanied them, or they may wish to avoid scrutiny. One function of the VPTs is to work across clinical teams to improve ascertainment of ARAs. The result is that patients can be stratified according to the extent that they engage with the intervention.

Patients identified in the ED PMS data as having attended due to an assault, but with no further contact with the VPT.Patients identified in the ED PMS or VPT data as having attended due to an assault but did not further engage with the VPT.Patients identified in the ED PMS and VPT data and who engaged with the VPT.

The primary analysis concerns group 3. The reasons for patients not engaging are potentially related to underlying characteristics and in secondary analyses we will explore this. However, it is reasonable to assume that the 3 groups represent varying levels of intervention dose, and therefore secondary analyses and analyses using groups 1-3 will be informative.

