### Allocation

Intervention patients will be identified in the VPT data and will have attended intervention EDs (in Cardiff and Swansea), subject to the above inclusion criteria. Control patients will be identified in the EDDS, and ED attendance was not in an intervention ED.

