**Figure 1 figure1:**
[figure not shown]
Count of patients, by month, identified by the Cardiff violence prevention team (VPT) as attending due to a violence-related injury, with the number that subsequently engaged with the VPT.

Initial estimates from Cardiff VPT suggest that 3% of those engaging with the VPT reattended ED at least once within one year, compared to 23% of patients who did not engage with the VPT. Data from 2015 and 2016 suggest that the frequency of unscheduled attendances for patients with at least one ARA (mean 2.35 attendances) is greater than for patients making an unscheduled attendance without evidence of an assault (mean attendances 1.73). For a simple Cox survival model, (α=.05; β=.90), and a hazard ratio of 0.8, a total N of 845 is required.

To realize the recurrent nature of analyses, simulation [44] (1000 estimates per point estimate) was used across varying follow-up periods, which suggests a 12-month follow-up period and total N of 300 is adequate to identify a significant effect. By increasing the number of controls, statistical power will be further enhanced [45].

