##### Matching

It is not possible to manipulate allocation to treatment, and we therefore rely on quasi-experimental methods to infer treatment effects. The purpose of matching control and intervention patients is to allow derivation of the average treatment effect under the assumption that allocation is not conditional on observed confounders. Matching on values of covariates between the treated and untreated groups avoids the bias introduced by covariates that influence the outcome variable. The goal being to find a subset of data that is closest to an exact match on observed covariates [53]. The primary analysis will be conducted using coarsened exact matching, with a minimum 1:1 ratio, with secondary analyses undertaken using propensity score matching.

For categorical covariates, exact matching is a sensible alternative. Here a match is considered acceptable only if the values of all covariates are equal between treated and untreated potential matches. Continuous covariates can, for the purpose of using exact matching, be turned into categorical covariates by defining category intervals; the resulting method is called coarsened exact matching. For matching, covariate categories can be grouped together to form larger (and fewer) categories, improving efficiency [53-55]. This approximates to a fully blocked experiment and requires temporarily coarsening variables.

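### The primary Objective 1 contrast sets VPT engagers against matched patients at other EDs whose willingness to engage is unobserved, so an inert VPT could show a benefit

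*Protocol article*

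**What the plan says.** Under Objective 1: Effectiveness (Design and Conceptual Framework), assault-related attenders at intervention EDs fall into three groups by extent of engagement. Group 3 is "Patients identified in the ED PMS and VPT data and who engaged with the VPT". The text then says: "The primary analysis concerns group 3. The reasons for patients not engaging are potentially related to underlying characteristics". Non-engagement is left to secondary analyses, and the three groups are treated as graded doses of the intervention.

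Allocation defines the comparison group: "Control patients will be identified in the EDDS, and ED attendance was not in an intervention ED". Aims and Objectives implies that controls also have an initial assault-related attendance (ARA). Matching makes coarsened exact matching on observed covariates primary, with at least one control per case, and propensity score matching secondary. It says this yields the average treatment effect "under the assumption that allocation is not conditional on observed confounders". Discontinuous Risk Interval adds a random effect, motivated by operational differences between Local Health Boards.

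Design and Conceptual Framework gives the calendar: "Intervention data collection therefore begins in November 2019 and ends in August 2023". It also says of the emergency department data set (EDDS) that "these data are consistent and available from January 2012". A difference-in-difference model is named for Objective 2.

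Sampling reports that 77% of 2312 contacted patients accepted support, and that "3% of those engaging with the VPT reattended ED at least once within one year, compared to 23% of patients who did not engage".

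For Objective 3, Exposure Variable is engagement with the VPT, whereas Cost-Effectiveness Analysis Outcomes reports results for patients offered against not offered VPT assessment.

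**The concern.** Cases are selected on what they did after being contacted; controls are not. At a control ED there is no offer to accept, so the matched controls mix people who would have engaged with people who would not. If those who engage were at lower risk of reattendance anyway, engagers will do better than controls even if the VPT changes nothing.

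A site problem lies on top of this. In the post-launch contrast every case comes from Cardiff or Swansea and every control from elsewhere, so exposure does not vary within an ED. A Health Board random effect cannot separate the VPT from other features of those two EDs. Usual Care adds a possible case-mix difference: "The patients eligible for VPT support are therefore those who are not eligible for support from the IDVA or ISVA". No parallel restriction on controls is stated in the article.

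At stake is what the main hazard ratio means. It would be read as the effect of the VPT and could support a national roll-out. The economic results are to be reported for offering the service, and an effect in engagers alone does not estimate that.

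**Working it through.** **Inputs (all from Sampling unless noted).** Engagement share a = 0.77 (acceptance among those contacted at Cardiff; assumed to equal the share who would engage at control EDs). One-year reattendance 0.03 in engagers and 0.23 in non-engagers. Planned hazard ratio (HR) 0.8, alpha 0.05, 90% power (printed as β = .90). Expected engagers 2500 + 900 = 3400, with 3400 controls at the minimum 1:1 ratio in Matching.

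**The plan's own figure.** Schoenfeld, two-sided: 4 × (1.960 + 1.282)² / (ln 0.8)² = 42.03 / 0.0498 = 844.1, rounded up to 845. The stated 845 reproduces (strictly as a number of events), so HR 0.8 is the benchmark.

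**Crude gap.** ln(0.97) / ln(0.77) = 0.0305 / 0.2614 = 0.117.

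**Whole gap is selection, VPT inert.**
- Control risk = 0.77 × 3% + 0.23 × 23% = 7.6%.
- Risk ratio = 3 / 7.6 = 0.39; HR from the risks = ln(0.97) / ln(0.924) = 0.385.
- Mixing rates instead: 0.117 / (0.77 × 0.117 + 0.23) = 0.36.

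**Part of the gap is selection, log-HR scale.** Let s be the share of the log HR that is selection and survives matching. Then r = 0.117^s and null HR = r / (0.77r + 0.23). Engager risk is 1 − 0.77^r (here 0.77 is the non-engagers' one-year event-free probability, 1 − 0.23), and control risk is the 77:23 mix. The chance of a significant benefit is Φ(√(d/4) × |ln HR| − 1.96), with d = 3400 × (engager risk + control risk).

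| s | r | engager / control risk | null HR | chance of false benefit |
|---|---|---|---|---|
| 100% | 0.117 | 3.0% / 7.6% | 0.36 | >99% |
| 75% | 0.199 | 5.1% / 9.2% | 0.52 | >99% |
| 50% | 0.341 | 8.5% / 11.9% | 0.69 | >99% |
| 25% | 0.584 | 14.2% / 16.2% | 0.86 | 68% |
| 10% | 0.807 | 19.0% / 19.9% | 0.95 | 16% |
| 0% | 1.000 | 23.0% / 23.0% | 1.00 | 2.5% |

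**Half the gap, risk scale.** Engagers 13%, non-engagers 23%: controls = 0.77 × 13% + 0.23 × 23% = 15.3%. HR = ln(0.87) / ln(0.847) = 0.84. Then d = 3400 × (0.130 + 0.153) = 962, √(962/4) × 0.176 = 2.73, and Φ(0.77) gives about 78%.

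**Selection that yields the planned 0.8 with no effect.** r = 0.8 × 0.23 / (1 − 0.8 × 0.77) = 0.184 / 0.384 = 0.479. Its share of the log HR is ln(0.479) / ln(0.117) = 34%. In risks this is 11.8% against 23%, or 11.2 of the 20 points (56%).

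**Recurrent-event check.** 1000 simulated null trials with 3400 per arm, gamma frailty of variance 1, and an assumed control mean of 1.35 reattendances (2.35 − 1):
- r = 0.5: rate ratio 0.81, 100% falsely significant.
- r = 0.7: rate ratio 0.91, 81% falsely significant.
- r = 1: rate ratio 1.00, 2.4% falsely significant.

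**Cost of not conditioning on engagement.** If the true HR is 0.8 in the 77% who engage:
- Equal baseline rates: 0.77 × 0.8 + 0.23 = 0.846, needing 1503 events for 90% power.
- r = 0.5: (0.77 × 0.5 × 0.8 + 0.23) / (0.77 × 0.5 + 0.23) = 0.875, 2349 events.
- r = 0.117: 0.944, 12,595 events.

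**The case against.** The authors state a hypothesis about engagement, acknowledge non-random engagement, match carefully and already plan analyses of groups 1-3. On that view the dispute is only over which analysis is primary. That is largely right, but the choice matters: the primary result is the one that will be quoted, and reading the groups as doses assumes the selection away.

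Several stronger readings are tempting and are not supported:

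- **That 0.39 is the expected bias.** It needs all of a crude, unmatched gap to be selection. The documents do not give the share. The 77% is among contacted patients, while the 23% may include patients never contacted, and nothing shows that 77% applies at control EDs. Nor does the bias shrink in simple proportion; it depends on the scale.
- **That controls are unselected.** They are matched and appear to have an initial ARA. They are only not selected on engagement.
- **That every bias favours the VPT.** Cardiff is the major trauma centre, Swansea is a trauma unit, and both VPTs took wider hospital and community referrals. Those differences could run either way, and more vulnerable patients might engage more.
- **That pre-2019 data are unused for Objective 1.** The article names a before-and-after contrast only for Objective 2 and is silent for Objective 1. Likewise, a control restriction matching the IDVA/ISVA rule may be in the full protocol.
- **That the hazard ratio passes straight into the economics.** The within-study analysis has its own fixed effects panel regression, although Objective 3 does base quality-adjusted life years on engagers against others.

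**Conclusion.** The concern stands. The primary contrast conditions on engagement in one arm only, on a characteristic that cannot be observed or matched on in the other, and the two arms share no ED. A hazard ratio below 1 therefore does not by itself distinguish an effective VPT from an inert one.

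The size is a range under stated assumptions, not an estimate: a null HR of 0.36-0.39 with full selection, 0.69 (log-HR scale) to 0.84 (risk scale) with half, and 1.00 with none. About a third of the log-HR gap, equivalent to 56% of the risk gap, reproduces the planned 0.8 with no effect. With 3400 per arm, even a quarter of the log-HR gap gives a 68% chance of a falsely significant benefit. This rests on 77% applying at control EDs and on the direction suggested by the Cardiff figures, which is probable but not certain.

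Two related faults are of wording. The matching assumption as printed omits the condition that matters, no unobserved confounding given the matched covariates. Matching controls to treated patients targets the effect in the treated rather than the average treatment effect. Neither alone changes an analysis.

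**What to change.** 1. Make the already planned groups 1-3 analysis primary or co-primary: all ARA patients coded in the ED patient management system at Cardiff and Swansea against ARA patients so coded at control EDs, matched on index period and prior unplanned ED attendances. Leave out patients found only in VPT data, since control EDs have no equivalent source.
2. Use the pre-launch EDDS data to estimate a launch-by-site effect with ED fixed effects. Add a sensitivity analysis for a change in ARA ascertainment at launch, because Objective 2 hypothesises exactly that, and it would alter the case mix of coded patients.
3. Report group 3 against controls as secondary, labelled as subject to engagement selection. Do not derive a per-engager effect by scaling the hazard ratio by the engagement share: hazard ratios do not scale that way, and VPT staff training may also affect non-engagers.
4. In Matching, state the assumption as no unobserved confounding given the matched covariates, and the estimand as the effect in the treated.
5. Results says the Objective 1 analyses were completed in August 2025, so disclose the change as post hoc and show both analyses.

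Cost: extra analysis of data already held in SAIL, and dilution. A true 0.8 in engagers becomes about 0.85 at 77% engagement with equal baseline rates, and weaker if engagers are at lower risk or if many group 1 patients had no VPT contact. Pre-launch years add patients, but the documents do not show whether that offsets the loss, so power should be recalculated.

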### Data

#### Violence Prevention Team Data (Cardiff and Swansea)

Intervention sites record patient details (name, date of birth, and gender), NHS number, extent of engagement with the VPT, and whether any subsequent referral was made.

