##### Exposure Variable

The exposure variable consists of patients engaging with the VPT.

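### The three engagement groups overlap, leave one kind of patient out, and cannot be read as intervention dose because they differ in who was reached and who accepted

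*Protocol article*

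**What the plan says.** The Methods subsection on Objective 1 (Protocol article, Design and Conceptual Framework) stratifies patients by how far they engage with the VPT:

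- Group 1: "Patients identified in the ED PMS data as having attended due to an assault, but with no further contact with the VPT".
- Group 2: "Patients identified in the ED PMS or VPT data as having attended due to an assault but did not further engage with the VPT".
- Group 3: "Patients identified in the ED PMS and VPT data and who engaged with the VPT".

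It then states: "The primary analysis concerns group 3". It concedes that "The reasons for patients not engaging are potentially related to underlying characteristics and in secondary analyses we will explore this". The next sentence nevertheless holds that "it is reasonable to assume that the 3 groups represent varying levels of intervention dose", and concludes that secondary analyses and analyses using all three groups will be informative.

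Two other places bear on this. For Objective 3 the protocol states: "The exposure variable consists of patients engaging with the VPT". Under the VPT data heading, sites are said to record "extent of engagement with the VPT, and whether any subsequent referral was made".

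**The concern.** There are two problems.

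The first is definitional. A stratification needs each patient to fall into exactly one stratum. The word joining the two data sources in group 2 lets group 1 patients in, and the word joining them in group 3 shuts some engagers out.

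The second is inferential. Dose language invites the reader to take an ordered pattern of outcomes across groups 1 to 3 as support for a causal effect. What moves a patient from one group to the next is whether the VPT reached or recorded them, and whether they accepted. Acceptance is the patient's own choice, and the protocol says it may be related to the patient's characteristics. Acknowledging that and then assuming dose in the next sentence leaves the interpretation unprotected. At stake is what the secondary analysis can conclude: it could show a gradient with no VPT effect, or blur a real difference by mixing decliners with patients never contacted.

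**Working it through.** **1. Group membership.** Take the assault-identified patients, classify each by presence in the ED patient management system (PMS), presence in VPT data, VPT contact and engagement, and apply the three definitions literally. Contact is taken to imply a VPT record, and engagement to imply contact.

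| PMS | VPT data | VPT contact | Engaged | Groups met |
|---|---|---|---|---|
| yes | no | no | no | 1 and 2 |
| yes | yes | no | no | 1 and 2 |
| yes | yes | yes | no | 2 |
| no | yes | no | no | 2 |
| no | yes | yes | no | 2 |
| yes | yes | yes | yes | 3 |
| no | yes | yes | yes | none |

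Both rows that meet group 1 also meet group 2, so group 1 lies wholly inside group 2. The last row fits nowhere. The protocol itself expects VPT-only identification: Objective 2 counts an assault attendance at intervention sites if it appears in either source.

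**2. Exposure by the protocol's own definition.** The Objective 1 hypothesis and the Objective 3 exposure variable both rest on engagement. On that definition groups 1 and 2 are both unexposed and only group 3 is exposed. Group 2 is not free of all contact, however. The Sampling section reports that Cardiff contacted 2312 patients, of whom 77% accepted:

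- accepted: 2312 × 0.77 ≈ 1780
- contacted but did not accept: 2312 × 0.23 ≈ 532

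**3. How far the literal overlap could dilute group 2.** Let U be the number of PMS assault patients with no VPT contact. The documents do not give U, so these values are assumptions. The share of group 2 that was contacted and declined is 532 / (532 + U):

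- U = 500: 532/1032 = 52%
- U = 1000: 532/1532 = 35%
- U = 2000: 532/2532 = 21%

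This applies only if the definitions are coded as written, and the 532 covers Cardiff to December 2022 only.

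**4. Can a gradient appear with no effect?** The Sampling section gives one-year reattendance of 3% in engagers and 23% in non-engagers. Under proportional hazards the crude hazard ratio is ln(0.97)/ln(0.77) = 0.12, far from the planning value of 0.8. That is compatible with selection but does not prove it.

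For an illustration, assume that 30% of contacted patients are high-risk, that one-year risks are 3% (low) and 23% (high), that overall acceptance is 77%, and that the VPT has no effect. Let OR be the odds of acceptance in high-risk relative to low-risk patients. Acceptance probabilities aL (low-risk) and aH (high-risk) solve 0.7·aL + 0.3·aH = 0.77. Then:

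- engaged risk = (0.7·aL·0.03 + 0.3·aH·0.23) / 0.77
- declined risk = [0.7·(1−aL)·0.03 + 0.3·(1−aH)·0.23] / 0.23
- apparent hazard ratio = ln(1 − engaged risk) / ln(1 − declined risk)

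| OR | aL | aH | Engaged risk | Declined risk | Apparent HR |
|---|---|---|---|---|---|
| 1 | 0.77 | 0.77 | 9.0% | 9.0% | 1.00 |
| 0.5 | 0.81 | 0.68 | 8.3% | 11.4% | 0.72 |
| 0.25 | 0.85 | 0.58 | 7.6% | 13.8% | 0.53 |
| 0.1 | 0.90 | 0.47 | 6.7% | 16.8% | 0.37 |

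The true hazard ratio is 1.00 in every row.

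The sample-size figure of 845 does not depend on this point.

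**The case against.** The strongest reply has four parts.

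- **Some ordering of exposure is arguable.** The VPTs also train staff, raise awareness and improve identification, so group 1 patients attended departments where that activity was in place. Group 2 includes patients whom the VPT contacted. This stands to the extent that a reader who infers that groups 1 and 2 both received nothing goes beyond the text: group 2 is described as not engaging *further*, and about 532 Cardiff patients were contacted without accepting. The supportable statement is that neither group engaged. The ordering remains confounded by reach and acceptance.
- **Selection is disclosed and the analysis is secondary.** Both are true. The primary analysis uses group 3 against matched controls from other departments, so its contrast is not directly changed. Disclosure does not justify the dose assumption that follows it.
- **The protocol makes no dose-response claim.** It specifies no trend test and calls these analyses only informative. A reader might infer that they are meant to corroborate the primary result, but the text does not say so. Nor do the documents show that any gradient would simply reflect who declines. They show only that selection and effect cannot be told apart, and a difference between groups 1 and 2 would also reflect who was reached.
- **The overlap is a drafting matter in a condensed article.** Exclusive groups were probably intended, and the full protocol may contain coding rules. However, the article states the definitions, and as stated they cannot be applied.

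**Conclusion.** The point holds as a defect in a secondary analysis. By logic alone, group 1 is contained in group 2 and VPT-only engagers are unclassified. By the protocol's own definition of exposure, groups 1 and 2 are both non-engaged. The step from degree of engagement to dose has no stated support and sits against the protocol's own caveat about who engages.

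The size of any distortion cannot be fixed from the documents. The apparent hazard ratios of 0.72 to 0.37 rest on the assumed 30% high-risk share, the assumed stratum risks and the assumed acceptance odds. The 52% to 21% range rests on assumed counts of uncontacted patients. They show that a gradient can arise, or be diluted, without any change in the VPT effect. They do not show that this happened.

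**What to change.** 1. Define exclusive and exhaustive groups: (1) assault recorded in the PMS with no VPT contact; (2) VPT contact recorded but not engaged; (3) engaged, with a stated rule for engagers found only in VPT data. Also say where patients go who have a VPT record but no contact.
2. Delete the assumption that the groups represent levels of intervention dose.
3. Report differences across the groups as descriptive of reach and selection, not as dose-response.
4. If outcomes are examined among engagers by recorded extent of engagement or referral, label the analysis exploratory and post hoc, and state that it carries the same selection: extent is partly the patient's choice, and referral may track need.

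The cost is more than wording. The Results section reports the Objective 1 analyses complete in August 2025, so a secondary analysis may need to be re-run with the revised groups, or at least re-labelled. The fields for extent of engagement and referral are already recorded by the sites, so no new collection is needed for step 4.
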